#### Blinding description

Participants were divided into intervention and control groups (delayed-intervention group) after obtaining informed consent. Trials were planned so that participants were aware of all the aims of the study. Based on the research group’s planning, all members of the intervention and delayed-intervention groups accessed all education. The intervention group members were initially educated, and the members of the delayed-intervention group received training 3 months after receiving the post-test results. It is necessary to mention that students were unaware of assignments in the study groups.

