### Processes

#### Schools of university

First, university permission to conduct the study was obtained. University administrators would access questionnaires for an estimate if demanded. Efforts were made to balance the inclusion of both state and non-state universities, as well as to range in their socio-demographic characteristics. Based on the previous formative research [27] and random sampling of Hamadan universities, 3 universities were expected to participate. Therefore, the number of students in each school or university was obtained by proportional assignment of students to the school (i.e., the school with the largest number of students, the largest number of students assigned). After coordinating with university officials, the research units were rationed. Then, the samples were randomly collected.

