#### Students

It was anticipated that up to 161 students might be enrolled in this study. Research team members explained the aims of the survey to students and distributed consent forms. Students were eligible to participate if they were members of Hamadan universities and consented to receive SAML and substance abuse prevention education. Students completed consent and permission forms, respectively, before initiating the study.

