The pairing of preventive substance abuse information and SAML education allows the program to teach students critically thinking about media messages related to substance abuse specifically marijuana and substance abuse behaviors. It mostly teaches them what lifestyles, values, and points of view are represented in or omitted from media messages about substance abuse, such as identification and the possible implications of actual consumption of drugs, including simulating an actor, having instant excitement, believing in the non-addictive nature of advertised substance, and having ideal moods and herbal and not harmful effects.

Education consisted of 5 web-based education sessions about substance abuse prevention and SAML. Each session included 40–45 min of training with the question-and-answer methods. Group discussions (chat rooms) were held with multimedia tools and reminder messages, such as the first educational session to familiarize students with drugs, especially marijuana and substance abuse behavior consequences. The second session aimed to educate students on SAML skills, critical thinking, and media consumption regime. The third session aimed at familiarizing students with interpersonal skills and self-awareness, and the fourth session taught students how to say no and how to solve problems. The fifth session corrected students’ beliefs and attitudes toward substance abuse using the mentioned web-based teaching methods and materials—each containing group discussion in chat rooms. The intervention group received lessons between completing the pretest and follow-up (Fig. 3). The website contained an educator dashboard for educators. They will be one of the research teams to enroll the students in the program and group discussions, including chat rooms, to correct their beliefs about drugs. Educators were also allowed to use web-based education programs in order to make education programs more accessible to students. All educators were requested to review all of the materials.

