#### Delayed-intervention group

Students in the delayed-intervention group received lessons during the study, but educators were requested to abstain from any substance abuse or SAML topics. Simultaneously, educators in the delayed-intervention group did not train them until after study completion (i.e., collecting student data at a 3-month follow-up).

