#### Implementation procedure

As mentioned previously, participants in this study were familiar with e-learning classes and online education due to the COVID-19 pandemic. Educators accessed the web-based educator’s control panel, giving them access to programs. The principal investigator and the research team visited the website. Privacy shields were provided to block their computers or tablet screens from view to ensure confidentiality. Secret ID numbers were used in place of names in chat rooms, and during receiving education programs, admin and educator sessions were offered to students before education. Students were instructed that they could withdraw from the study at any time for any reason. Follow-up questionnaires were completed with paper copies of the pretest questionnaire. After completing the data collection, educators in the intervention group provided substance abuse prevention and SAML education over 3 weeks. It was predicted that the program could be completed in 5 45-min sessions. In the follow-up period, students in the intervention group gave their feedback on the program. Educators returned all completed follow-up questionnaires to administer and Principal Investigator after approximately 3 months. After collecting the follow-up data, educators in the delayed-intervention group could provide SAML and substance abuse prevention education to students and give feedback on their experiences.

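### Students are described as unaware of their group, but the design cannot blind them at follow-up, and all outcomes are self-reported on forms returned by educators

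*Protocol article*

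**What the plan says.** All references are to the protocol article.

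- **Blinding description:** "students were unaware of assignments in the study groups". The same paragraph says "Trials were planned so that participants were aware of all the aims of the study", and that the intervention group is educated first and the delayed-intervention group later.
- **Students:** eligibility requires that students "consented to receive SAML and substance abuse prevention education".
- **The intervention description:** "The intervention group received lessons between completing the pretest and follow-up". There are five sessions, and the last is aimed at changing beliefs and attitudes about substance abuse.
- **Delayed-intervention group:** these students have lessons during the study, but "educators were requested to abstain from any substance abuse or SAML topics", and "educators in the delayed-intervention group did not train them until after study completion", which the section ties to collection of the 3-month data.
- **Student measures and Outcome measures:** the outcomes come from a questionnaire of about 100 items that the student fills in. It covers substance abuse behaviour, the prototype willingness constructs and the substance abuse media literacy (SAML) scale.
- **Implementation procedure:** follow-up is on paper, the intervention-arm educators do the teaching, and "Educators returned all completed follow-up questionnaires to administer and Principal Investigator after approximately 3 months".
- **Blinding description and Fidelity of implementation process:** both also say, in different words, that all students had access to all of the education.

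**The concern.** A blinding statement tells the reader how far to trust outcomes that depend on the participant's judgement. Here that covers every outcome: attitude, norms, willingness, intention, reported use and self-rated media literacy. A student who knows the aims and has just been taught why drug use is undesirable knows which answers are approved. A control student has had no such sessions before follow-up. If taught students shade their answers more than controls do, the between-group comparison mixes a change in reporting with a change in behaviour or intention, and the planned tests cannot separate the two.

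The return route may add to this, because completed forms pass through educators and only the intervention-arm educators have delivered the prevention message by then.

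This is not a detail left to a fuller protocol or an analysis plan. The article affirmatively claims a property that its own design excludes, and a reader would credit the trial with participant blinding that it does not have.

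**Working it through.** No figure in the plan is at issue, so the check sets the sections side by side.

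**1. What a student knows before the first session.** The student knows all the aims (Blinding description) and has consented to receive this named education (Students).

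**2. What a student experiences before follow-up.** In the intervention arm, five sessions on substance abuse and SAML fall between pretest and follow-up (The intervention description). In the delayed arm, there are other lessons with these topics withheld until the 3-month data are in (Delayed-intervention group). The Blinding description itself has one group taught first and the other later.

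**3. Combining 1 and 2.** At follow-up, a student who knows that the trial concerns this education and has, or has not, received it can tell which group he or she is in. The unawareness statement could be true of the moment before assignment, which is concealment of allocation. It cannot be true when the outcomes are recorded.

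**4. Do the access statements change this?** Read literally, access to all education for all students conflicts with withholding it from the delayed arm. If it means access eventually, step 3 stands. If it means access before follow-up, the contrast between the arms is itself in doubt. Neither reading creates blinding, so these passages must be reconciled.

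**5. Exposure of the outcomes.** All are completed by the student. The fifth session targets beliefs and attitudes, and attitude is a measured construct. The article describes neither an objective measure nor an independent data collector. Coded IDs and screen shields limit disclosure to others, but they do not hide the arm from the student, and screen shields do not cover a paper follow-up form.

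**6. Scale, under assumptions only.** The document gives no size for a reporting shift. Suppose that there is no true effect, that answers shift in one arm only, and that observations are independent (clustering ignored), with two-sided alpha 0.05. The group sizes of 54 and 58 come from Sample size and eligibility criteria.

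For a scale score with a reporting shift of d SD, the probability of a significant result favouring the intervention is about Φ(d·√(n/2) − 1.96).

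| n per group | d = 0 | d = 0.2 | d = 0.5 |
|---|---|---|---|
| 54 | Φ(−1.96) = 0.025 | Φ(1.039 − 1.96) = 0.179 | Φ(2.598 − 1.96) = 0.738 |
| 58 | 0.025 | Φ(1.077 − 1.96) = 0.189 | Φ(2.693 − 1.96) = 0.768 |

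For reported use, take an assumed control proportion p of 20% to 50% and a proportion q = p − b in the taught arm, with p̄ = (p + q)/2. The probability is about Φ{(b − 1.96·√[2p̄(1 − p̄)/n]) / √[(p(1 − p) + q(1 − q))/n]}. With b = 10 points and n = 54:

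- p = 0.20: Φ{(0.100 − 0.135)/0.068} = 0.305
- p = 0.50: Φ{(0.100 − 0.188)/0.095} = 0.179

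The probability rises slightly from 54 to 58 per group, so a larger trial would not remove the problem. These figures show only what an assumed shift would do. They are not an estimate for this trial.

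**The case against.** The strongest reply is that lack of participant blinding and reliance on self-report are inherent in an educational trial, so what remains is a sentence to correct and a limitation to state. Much of that stands: the design need not be abandoned. It does not save the sentence, which sits under a blinding heading and is not limited to the time before assignment.

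Four stronger readings are tempting, and the document does not support them.

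- **That the teaching educators collect and read the answers.** The text says that they returned the completed forms. It does not say how students handed them in, whether the forms were sealed, or whether educators could see the content. Only passage through their hands is established.
- **That the return route differs by arm.** Educators return all the follow-up forms, and the delayed arm has educators too. What differs is that the intervention-arm educators have already delivered the prevention content. Differential reporting is therefore a plausible inference, not a demonstrated fact.
- **That control students are taught nothing.** They receive lessons without this topic.
- **That administrators' access breaks the confidentiality promise.** Schools of university says "University administrators would access questionnaires for an estimate if demanded". That sentence directly follows obtaining permission from the university, so review of the blank instrument is a natural reading. The restrictions in the retention and Confidentiality sections cover the key linking names to IDs, not the questionnaires. The sentence is ambiguous, but it contradicts neither section.

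**Conclusion.** The concern holds in this limited form. Students cannot be unaware of their group at follow-up, so the blinding statement is wrong as written; at most, allocation was concealed until assignment. Because every outcome is self-reported and the completed forms pass through educators, socially desirable reporting may differ between arms and may appear as a treatment effect on attitude, willingness, intention or use.

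The contradiction rests on the article's own text and needs no assumption about size. The direction of any bias is an inference, and its amount cannot be estimated from the document. The probabilities in the working depend wholly on the assumed shift. A reader might infer that the results are known to be biased, or biased by a stated amount; the document supports neither.

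**What to change.** 1. **Blinding description:** describe the trial as open-label for students and educators. If it is true, say that allocation was concealed until assignment.
2. **Access to the education:** reconcile the universal-access statements in Blinding description and Fidelity of implementation process with Delayed-intervention group, stating who could reach which material before the 3-month follow-up.
3. **Return of follow-up forms:** in both arms, have questionnaires submitted under the study ID, either sealed or online without access from the educator dashboard. They should go to existing study staff who do not teach and do not hold the name-ID key. Staff who hold that key should not receive the forms, since answers and identities would then be in the same hands.
4. **Conclusions:** state that all outcomes are unblinded self-report.
5. **Schools of university, as a clarification only:** if it is so, say that administrators see the blank questionnaire.

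Items 1, 2, 4 and 5 cost only wording and can be done even if data collection has ended. Item 3 applies if follow-up is still open. It needs a changed return route and possibly a reassignment among existing staff, but no larger sample and no new measure.

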#### Fidelity of implementation process

These educations started and ended based on research team planning. The real lessons of the online session were accessible to all students without any limitations.

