**Methods:**

The present study evaluates an intervention program based on media literacy on substance abuse prevention among students using an integrated social marketing approach. This study aims to complete the SMART model’s sixth and seventh stages, implementing intervention and evaluation. Participants will be students of Hamadan University, Iran. Randomization will occur at the university and school levels, and gathered data will appear at two-time (i.e., pre-test and three months follow-up). Intervention group students will obtain both substance abuse prevention education and substance abuse media literacy (SAML) education between pre-test and 3 months post-test. Students in the delayed intervention will be given this education after study accomplishment; this group will receive their regular courses except for substance abuse prevention and media literacy titles during education intervention. The outcome variables are intentions and substance abuse behavior based on prototype willingness and substance abuse media literacy.

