#### The intervention description

As noted based on the previous formative-mixed methods research, materials, the content of interventions, and the type of delivery channel to participants (which was based on audience tendencies) were identified and developed, and interventional education was developed by an interdisciplinary group consisting of specialists in psychology, media research, web site development, multimedia design, and health education and promotion.

SAML and preventive substance abuse educations were web-based and comprehensive education programs for university students, providing appropriate and medically accurate information about substance abuse using a media literacy education approach. It should be noted that this interventional education would be web-based because of the COVID-19 pandemic to comply with health protocols in Iran. Some advantages of this approach are as follows: Because of the COVID-19 pandemic and social-distancing measures in Iran, it is not clear when universities can return to normal education situations and face-to-face educational interventions. Thus, a web-based approach to delivering education interventions in person was selected. Also, this approach allows for a fully interactive environment or 2-way forms of communication, often between individuals who know each other (e.g., friends) and may have a strong influence on behavior. Moreover, the health of participants is valuable and important for all researchers.

Also, the web-based channel was based on audience preferences and provided more access to materials for interventions. This channel is more flexible, and students can access it at all times and any place, and any individual concerning personal conditions can educate and use educational materials.

Some disadvantages of this approach are as follows: access to comprehensive materials and support can be difficult, and this approach requires additional training before starting educational interventions.

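### The fidelity section opens the online lessons to all students without limit, which as written conflicts with withholding them from the delayed-intervention group until the 3-month data are in

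*Protocol article*

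**What the plan says.** Two sets of statements in the protocol article bear on who could use the lessons before follow-up.

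**Open access.** Fidelity of implementation process: "The real lessons of the online session were accessible to all students without any limitations". The intervention description says of the web channel that "students can access it at all times and any place". The paragraph after Figure 3 in the same section says that students had the education until the semester ended, and does not say which group is meant.

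**Withheld education.**
- Abstract, Methods: "Students in the delayed intervention will be given this education after study accomplishment".
- Delayed-intervention group: "educators were requested to abstain from any substance abuse or SAML topics", and "educators in the delayed-intervention group did not train them until after study completion", with study completion explained there as collection of the 3-month student data.
- Implementation procedure: "After collecting the follow-up data, educators in the delayed-intervention group could provide SAML and substance abuse prevention education to students".
- Blinding description: "all members of the intervention and delayed-intervention groups accessed all education", followed at once by the order of delivery, in which the intervention group is taught first and "the members of the delayed-intervention group received training 3 months after receiving the post-test results".

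**The concern.** The trial's only contrast is education against delayed education at 3 months. It depends on the delayed group not having had the lessons when its follow-up questionnaire is filled in. The section on fidelity is where a reader would look for how the arms were kept apart, and it says the opposite without qualification.

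The safeguards that are described act on educators: they were asked to avoid the topics, and they did not teach the delayed group until the data were in. Neither governs whether a student can open a website. If some controls did use the lessons, the arms would move closer together and the effect would be biased toward no difference. A small or null result would then be harder to read, because it could reflect either a weak programme or a diluted comparison.

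**Working it through.** **Step 1. Does the text conflict?**

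| Section | Who has access | When |
|---|---|---|
| Fidelity of implementation process | all students | no limit stated |
| The intervention description, after Figure 3 | students, arm not named | to end of semester |
| Abstract, Methods | delayed group | after the study |
| Delayed-intervention group | delayed group | after 3-month data |
| Implementation procedure | delayed group | after follow-up data |
| Blinding description, both sentences | both groups | intervention group first, delayed group after the post-test |

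The first row, taken literally, cannot hold together with the Abstract, Delayed-intervention group and Implementation procedure rows. The second row is ambiguous. The last row agrees with the withheld-education plan: everyone is eventually taught, in sequence.

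**Step 2. Does anything else close the gap?** Three features might act as a gate.
- The intervention description has a member of the research team enrol students in the programme, but does not restrict enrolment to one arm before follow-up.
- Oversight and monitoring says that ID numbers were used to receive the education. The retention section gives IDs to participants generally after consent, and their stated purpose is confidentiality. They are not tied to arm.
- Implementation procedure describes a control panel for educators and sets no student permissions by group.

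None of these says that delayed-group students were locked out.

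**Step 3. Is exposure plausible?** Participant characteristics and Randomization assign individuals within university strata, so both groups share campuses. The Abstract instead places randomisation at university and school level, under which mixing would be less likely. Under Students, eligible students had agreed to receive this education. Under Blinding description, they knew the study aims but not their assignment.

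**Step 4. What could it cost?** The documents give no contamination rate, so the fraction c below is assumed.

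Inputs from Sample size and eligibility criteria: 20% effectiveness (taken here as p1 − p2 = 0.20), alpha 5% (two-sided, since the formula uses Z at alpha/2), 90% power, clustering coefficient 1.5, 54 per group.

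The plan's own figure comes first. (1.960 + 1.282)² = 10.507, so the printed formula times 1.5 is 1.5 × p̄(1 − p̄) × 10.507 / 0.04. This equals 54 only if p̄ is about 0.164 (36.0 × 1.5 = 54.0), a value the article does not state. Across p̄ from 0.10 to 0.50 it gives 35 to 99. The 90% is therefore nominal and is taken at face value below. The sample-size calculation is a separate matter.

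If a fraction c of controls uses the lessons and gains the full effect, the difference becomes 0.20 × (1 − c). Then power = Φ(√10.507 × (1 − c) − 1.96) = Φ(3.2415 × (1 − c) − 1.96), and the number per group needed to restore 90% is 54 / (1 − c)², before attrition.

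| Assumed c | Difference | Power | Per group for 90% |
|---|---|---|---|
| 0 | 0.20 | 90% | 54 |
| 10% | 0.18 | 83% | 67 |
| 20% | 0.16 | 74% | 85 |
| 30% | 0.14 | 62% | 111 |
| 50% | 0.10 | 37% | 216 |

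For example, at c = 20%: 3.2415 × 0.8 − 1.96 = 0.633, and Φ(0.633) = 0.737.

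**The case against.** The strongest reply is that the fidelity sentence is loose wording. The sentence before it says that the education began and ended as the research team planned, and in a section on fidelity, all students may mean all students receiving the programme. Sessions were scheduled, with chat rooms, enrolment by the team and ID numbers, which suggests some control of entry. This is a fair reading of intent and may well be correct. But the text does not say it, and no feature cited is tied to study arm, so the wording still has to be reconciled.

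Two stronger readings are tempting and are not supported.
- A reader might take the Blinding description's statement that both groups accessed all education as a second contradiction. Its next sentence puts the delayed group after the post-test, so it supports the sequential plan.
- A reader might infer that the comparison was in fact contaminated. The documents report no control access. They show only that nothing stated prevents it.

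It is also fair to say that a condensed article need not describe website logging. The absence of an access measure is therefore not an error in itself. The point rests on an affirmative statement that contradicts the control condition.

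**Conclusion.** The concern holds as a conflict in the text and an unguarded risk. The fidelity sentence, read as written, is incompatible with the withheld-education control in three other places, and the end-of-semester sentence leaves the arm unclear.

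Any resulting bias would be toward no difference. This assumes that the lessons work in the intended direction and that some controls used them. Its size is unknown. The power figures illustrate sensitivity and do not estimate what happened: they assume a contamination rate, give each exposed control the full effect, and start from a nominal 90% that cannot be reproduced without an unstated p̄. The sharing argument also depends on individual randomisation within universities, which the body text states and the Abstract does not. The point still deserves correction because it touches the trial's only contrast and is cheap to settle.

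**What to change.** Reconcile Fidelity of implementation process and the end-of-semester sentence after Figure 3 with the Abstract, Delayed-intervention group, Implementation procedure and Blinding description.

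1. State that lesson access is limited to the intervention group until the 3-month questionnaire is collected, and name the group to which end-of-semester access applies.
2. Enforce this with logins tied to the ID numbers already issued.
3. Report any control-group access with the main result, from the website log or from one added question at follow-up.

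If follow-up is already complete, correct the wording to say who had access and when, and report whatever access records exist.

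The cost is a small website set-up task and one more item on a questionnaire of about 100 items. Controls lose early sight of the material, which the delayed-intervention plan already intends.
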